### ***Randomization and Concealment***

Patients are randomly allocated to interventional or control group by drawing sequentially numbered, coded, sealed, opaque envelopes, each containing the group assignment of either interventional or control. The sealed envelopes for randomization will be prepared by a third party who takes no further part in the study. The ITPB syringes are prepared under strict asepsis by a nurse not involved in the study. ITPB is performed by a single anaesthesiologist who is blinded to group allocation. The primary care team, blinded to group allocation, performs surgeries using standardized technique. Anaesthesiologists and nurses blinded to group allocation recorded data intraoperatively, in the ICU, and at regular intervals in cardiac wards. Data will be recorded at 2-hour, 4-hour, 8-hour, 12-hour, 24-hour, 48-hour and 72-hour after extubation and at 1-month, 3-month, 6-month and 12 months after surgery by blinded personnel.

### ***Anaesthesia and Interventions***

All patients receive standard cardiac surgery monitoring. General anaesthesia is induced with midazolam 0.01-0.05 mg/kg, fentanyl 2-5 mcg/kg, and rocuronium 0.5-1 mg/kg to facilitate intubation. Anaesthesia is maintained with sevoflurane and propofol infusion, targeting a Bispectral Index of 40-60. ITPB is performed after anaesthesia induction with the patient in lateral decubitus positioning. Intraoperative opioids (fentanyl and morphine) will be administered at the discretion of the anaesthesiologist. The postoperative analgesia protocol was identical in both study groups, including patient-controlled analgesia (PCA) morphine protocol for 72 hours after surgery, oral analgesics (paracetamol 1g every 6 hours, dihydrocodeine 30mg three times a day), and on-demand antiemetics (intravenous ondansetron 4mg every 8 hours). Rescue analgesics on top of the protocol regimen can be prescribed as needed. Upon ICU admission, propofol infusion is stopped to facilitate weaning from ventilator using Adaptive Support Ventilation (ASV), which adjusts the ventilation parameters depending on the patient's lung mechanics and effort. Pain will be assessed regularly in ICU and on the ward. Upon extubation, pain scores are assessed at 2-hour, 4-hour, 8-hour, 12-hour, 24-hour, 48-hour and 72-hour. Patients receive PCA morphine for moderate to severe pain. Nausea, vomiting and rescue antiemetics are documented.

### ***Ultrasound Block Placement***

The intervention group received bilateral ITPB after GA induction, whilst sham blocks are performed in the control group. All blocks are performed by an anaesthesiologist who had previously performed  $\geq 50$  successful ITPB blocks, using Philips EPIQ ultrasound system, with a curved array transducer (C5-1), and 80mm echogenic nerve block needle (SonoTAP; PAJUNK, Germany). ITPB is performed with the patients positioned in a lateral decubitus position. The target intervertebral level (T4-5) is identified and marked in the preview ultrasound scan. The transducer is placed 2-3 cm lateral to the spinous process. Under strict asepsis, a single-level (T4-5) ultrasound-guided ITPB is performed with the in-plane insertion of the block needle from lateral to medial direction until its tip is at the medial aspect of the retro-SCTL space. After confirming the needle position by distension of the retro-SCTL space after a test bolus injection of 1-2 ml 0.9% normal saline, 25 ml 0.25% levobupivacaine or placebo is injected via the nerve block needle in small aliquots. The same procedure is repeated on the other side with the same volume of study medication. The time required to perform the block will be recorded as the time from insertion of block needle to removal from the patient after injection.

***Outcome measures***

Though acute pain is identified as an important predictor for the development of CPSP, advanced pain management strategies have failed to reduce the overall incidence of CPSP, suggesting a complex underlying mechanism. Evidence has demonstrated that pain-related functional interference and patient-reported outcomes, such as quality of recovery, might be associated with the development of CPSP. Thus, the primary outcome of this study is the Quality of Recovery (QoR-15) score at 24 hours after extubation. QoR is recommended for patient's comfort after surgery, and is highly valid and reliable patient-centred outcome measure.

Secondary outcomes include Numerical Rating Scale (NRS) pain scores at 2-hour, 4-hour, 8-hour, 12-hour, 24-hour, 48-hour and 72-hour after extubation, patient satisfaction with pain management and postoperative morphine consumption at the above time points, the time for first morphine rescue (in minutes), intraoperative opioids consumption (converted into morphine equivalence), duration of mechanical ventilation, length of stay in ICU and hospital, side effects associated with opioids such as postoperative nausea and vomiting (PONV), incidence of CPSP at 3-month, 6-month and 12-month, and pain interference measured with Short-Form McGill Pain Questionnaire-2 (SF-MPQ-2) and Brief Pain Inventory (BPI) Interference Scale at 3-month, 6-month and 12-month after surgery.

CPSP is defined as persistent pain after surgery that was not present before surgery or that had different characteristics, and other possible causes of pain are excluded. Participants reported CPSP will further be assessed on the severity and impact of chronic pain based on the recommendations by the Initiative on Methods, Measurement, and Pain Assessment in Clinical Trials (IMMPACT), including the SF-MPQ-2 to assess the sensory pain qualities and affective components, and the BPI to assess the interference of pain with physical functioning.

Chinese version SF-MPQ-2 is used to measure the sensory and affective aspects of pain. It evaluates symptoms related to chronic pain on a 11-point numerical rating scale (0 = none, 10 = worst possible). There are three sensory descriptors and one affective descriptor. The four subscales will be calculated as a mean of items in each subscale, and the total score is calculated as the mean of all 22 items. Higher subscale or total scale scores indicate more intense symptoms. The Chinese version of the Brief Pain Inventory (BPI) Interference Scale is used

to evaluate the extent of pain interfering with various components of functioning, including physical functioning, emotional functioning and sleep.

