## Introduction

The cornerstone of modern pain management in cardiac surgery lies in proactively preventing the development of chronic postsurgical pain (CPSP). This paradigm shift emphasizes pre-emptive interventions to disrupt the cascade of events and central sensitization that transform acute postoperative pain into a persistent, debilitating condition. CPSP, a significant and often underestimated consequence of cardiac surgery, affects a substantial proportion of patients, with prevalence rates ranging from 28% to 56% in the years following surgery. Its impact extends beyond mere discomfort, significantly impairing daily function, reducing quality of life, and imposing a substantial economic burden on the healthcare system.

The pathophysiology of CPSP involves a complex interplay of factors, with central sensitization playing a pivotal role. This process, characterized by heightened neuronal excitability within the central nervous system, amplifies pain signals and can lead to persistent pain even after the initial injury has healed. Therefore, a crucial aspect of CPSP prevention lies in disrupting the afferent nociceptive signals transmitted from the injured tissues to the spinal cord and brain, thereby preventing the establishment and perpetuation of central sensitization.

While opioids have traditionally been the mainstay of postoperative pain management, their use is not without significant drawbacks. Opioids can have dose-dependent side effects, including respiratory depression, nausea, and constipation. Furthermore, prolonged opioid use can lead to tolerance, opioid-induced hyperalgesia, and an increased risk of chronic opioid use. Recognizing these limitations, the current emphasis in pain management is on multimodal analgesia strategies that incorporate non-opioid medications and regional anaesthesia techniques to optimize pain control while minimizing the risks associated with opioid use.

Non-steroidal anti-inflammatory drugs (NSAIDs) offer a valuable adjunct in pain management, but their use in cardiac surgery is often limited due to concerns regarding bleeding complications and potential renal impairment. Other non-opioid analgesics, such as paracetamol and gabapentinoids, have shown limited efficacy in managing the intense pain associated with sternotomy. Regional anaesthesia techniques have emerged as promising

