## Methods

This is a prospective, parallel, double-blinded, randomized controlled trial. Patients undergoing elective cardiac surgery in Prince of Wales Hospital, a university teaching hospital with 1650 beds in Hong Kong, are eligible for enrolment. All patients will be admitted to a 23-bed ICU for early postoperative care and monitored with 1:1 nursing at all times, with an expectation of discharge from ICU to a high-dependency cardiac ward within 24 hours after surgery. Currently, 350-400 adults undergo elective coronary artery bypass graft (CABG) and/or valvular surgery each year.

**Inclusion:** Adult patients aged 18 or older, undergoing elective CABG, valve repair/replacement, or combined CABG/valve procedure via sternotomy, will be included.

**Exclusion:** Emergency surgery, redo surgery, history of chronic pain or being on chronic opioids/sedatives, renal failure with an estimated glomerular filtration rate  $\leq 30$  ml/min (calculated by Cockcroft-Gault formula), re-operation within 24 hours after surgery, intraoperative use of remifentanyl, and inability to provide informed consent.

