### ***Data collection (Appendix A)***

After screening for eligibility, patients will be given information sheets regarding the main aspects of the trial and information will be discussed with the research nurse before informed consent is obtained. All data is collected by research team members blinded to group assignment. Patient demographics and body mass index are recorded. Cumulated opioid consumption data and time to first morphine rescue are extracted from PCA pump. At 2-hour, 4-hour, 8-hour, 12-hour, 24-hour, 48-hour and 72-hour post-extubation, pain scores at rest and on coughing are quantified using NRS from 0 to 10. Zero represents no pain at all while 10 points represents the worst pain ever. The patients are asked to rate the overall satisfaction to pain management on a verbal analogue scale (0=worst possible, 100=best possible) at the predefined points. Any nausea and vomiting, and use of rescue antiemetics are documented. The Chinese validated QoR-15 will be completed at baseline (preoperatively) and postoperatively at 24-hour and 72-hour after extubation. The SF-MPQ-2 and Brief Pain Inventory will be used to evaluate the CPSP at 3-month, 6-month and 12-month after surgery.

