## Appendix A

The following medical and surgical data during the hospital stays will be extracted from electronic record:

1. Patient demographics (age, gender, EuroScore)
2. Type of surgery
3. Duration of surgery and duration of cardiopulmonary bypass
4. ASV time to spontaneous breathing
5. Episodes of nausea and vomiting, and use of rescue antiemetics
6. Length of ICU and hospital stay

|                     |           | STUDY PERIOD    |             |             |             |              |              |              |              |         |         |
|---------------------|-----------|-----------------|-------------|-------------|-------------|--------------|--------------|--------------|--------------|---------|---------|
|                     | Enrolment | Post-allocation |             |             |             |              |              |              |              |         |         |
| TIMEPOINTS          | Baseline  | 2h extubate     | 4h extubate | 6h extubate | 8h extubate | 12h extubate | 24h extubate | 48h extubate | 72h extubate | 3-month | 6-month |
| ENROLMENT:   |           |                 |             |             |             |              |              |              |              |         |         |
| Eligibility screen  | X         |                 |             |             |             |              |              |              |              |         |         |
| Informed consent    | X         |                 |             |             |             |              |              |              |              |         |         |
| Demographic data    | X         |                 |             |             |             |              |              |              |              |         |         |
| Comorbidity data    | X         |                 |             |             |             |              |              |              |              |         |         |
| EuroScore           | X         |                 |             |             |             |              |              |              |              |         |         |
| Allocation          | X         |                 |             |             |             |              |              |              |              |         |         |

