| INTERVENTION |           |                 |             |             |             |              |              |              |              |         |         |
| ITPB                | X         |                 |             |             |             |              |              |              |              |         |         |
| OUTCOMES:    |           |                 |             |             |             |              |              |              |              |         |         |
| Presence of CPSP    |           |                 |             |             |             |              |              |              |              | X       | X       |
| SF-MPQ-2            |           |                 |             |             |             |              |              |              |              | X       | X       |

|                                           |   |   |   |   |   |   |   |   |   |   |
|-------------------------------------------|---|---|---|---|---|---|---|---|---|---|
| BPI                                |   |   |   |   |   |   |   |   | X | X |
| QoR-15                             | X |   |   |   |   | X |   | X |   |   |
| Intraoperative morphine equivalent |   | X |   |   |   |   |   |   |   |   |
| NRS score                          |   | X | X | X | X | X | X | X |   |   |
| ASV time to spontaneous breathing  |   | X |   |   |   |   |   |   |   |   |
| Time to first morphine rescue      |   | X | X | X | X | X | X | X |   |   |
| Postoperative morphine consumption |   | X | X | X | X | X | X | X |   |   |
| Patient satisfaction               |   | X | X | X | X | X | X | X |   |   |
| Use of rescue antiemetics          |   | X | X | X | X | X | X | X |   |   |
| Nausea/vomiting                    |   | X | X | X | X | X | X | X |   |   |
| ICU and hospital stay              |   |   |   |   |   |   |   |   | X |   |

**Appendix A** Assessments overview. NRS, numerical rating scale; ASV, adaptive support ventilation; QoR-15, Quality of Recovery questionnaire; BPI, Brief Pain Inventory; SF-MPQ-2, Short-Form McGill Pain Questionnaire

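### CPSP is defined against the patient's preoperative pain, but beyond the chronic-pain exclusion no preoperative record of pain site, intensity or character is scheduled

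*Protocol*

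**What the plan says.** The Outcome measures section gives the definition: "CPSP is defined as persistent pain after surgery that was not present before surgery or that had different characteristics". The rest of that sentence rules out pain that has another explanation. The Introduction uses the same definition and makes CPSP at 3 months the primary aim. Outcome measures lists CPSP at 3, 6 and 12 months among the secondary outcomes and names QoR-15 at 24 hours after extubation as primary.

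The timing of each relevant measure is set in Data collection and Appendix A:

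- **NRS:** seven assessments, at rest and on coughing, the first 2 hours and the last 72 hours after the tube is removed. None is preoperative.
- **SF-MPQ-2 and BPI:** the text reads "The SF-MPQ-2 and Brief Pain Inventory will be used to evaluate the CPSP at 3-month, 6-month and 12-month after surgery".
- **QoR-15:** according to the same section, this questionnaire "will be completed at baseline (preoperatively) and postoperatively at 24-hour and 72-hour after extubation". It is the only patient-reported instrument named before surgery.
- **Other baseline entries in Appendix A:** eligibility, consent, demographics, "Comorbidity data", EuroScore, allocation and the block itself. The row "Presence of CPSP" is marked only at follow-up.

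The exclusion criteria in Methods remove patients with a "history of chronic pain or being on chronic opioids/sedatives". Data collectors are blinded to allocation. The protocol does not say how preoperative pain is established, or how a change in its characteristics is judged.

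**The concern.** Both limbs of the definition look back to the preoperative state. The first asks whether pain was there at all, and the second asks whether it was a different pain. The second limb matters only for patients who had some pain before surgery, so the definition itself allows for such patients in the trial. For them, the schedule supplies no description to compare with.

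An assessor at 3 months or later would have only the patient's memory and whatever the notes happen to contain. Errors can go both ways: an old pain may be counted as new, or a new pain dismissed as old. A statistical analysis plan cannot repair this, because the preoperative state cannot be measured once the operation is over.

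At stake is the accuracy of CPSP at three time points, the outcome that motivates the trial in its Introduction.

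**Working it through.** **1. The plan's own calculation.** The protocol gives no sample size or power for CPSP. Its only calculation is for QoR-15 (difference 8, SD 12, two-sided 0.05, 80% power):

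n = 2 × (1.960 + 0.842)² × 144 / 64 = 35.3, so 36 per group, as stated. Allowing for 20% loss, 36 / 0.8 = 45, and the planned 48 covers this. CPSP classification does not enter this calculation, so it and the total of 96 are unaffected.

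**2. What the definition needs against what is scheduled.**

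| Needed before surgery | Scheduled source |
|---|---|
| Chronic pain present or absent | Eligibility screen (exclusion criterion) |
| Recent or intermittent pain present or absent | None named; comorbidity data are not described as covering it |
| Site and character of any pain | None |
| Intensity of any pain | None; NRS starts 2 hours after extubation |

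The gap is therefore confined to non-chronic preoperative pain.

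**3. Effect of misclassification.** Let p be the true CPSP risk, Se the sensitivity and Sp the specificity of the classification, equal in both arms.

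Observed risk = p × Se + (1 − p) × (1 − Sp)

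The observed risk difference is the true one times (Se + Sp − 1).

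**4. Illustration with false positives only (Se = 1).** The Introduction cites "prevalence rates ranging from 28% to 56% in the years following surgery". The mid-point, 42%, is taken as the control risk. The halving to 21% and all the error rates are assumptions; the documents give none. Power uses the normal approximation for two proportions, two-sided 0.05. It is shown for 48 per arm and for 38 per arm, the latter because the protocol plans for 20% loss after discharge (48 × 0.8 = 38.4).

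At 10% false positives, control is 0.42 + 0.58 × 0.10 = 47.8% and ITPB is 0.21 + 0.79 × 0.10 = 28.9%. The ratio is 28.9 / 47.8 = 0.60 and the difference is 18.9 points.

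| False positives | Control vs ITPB | Risk difference (points) | Risk ratio | Power, 48 per arm | Power, 38 per arm |
|---|---|---|---|---|---|
| 0 | 42.0% vs 21.0% | 21.0 | 0.50 | 60% | 50% |
| 1% | 42.6% vs 21.8% | 20.8 | 0.51 | 59% | 49% |
| 3% | 43.7% vs 23.4% | 20.4 | 0.53 | 56% | 47% |
| 5% | 44.9% vs 25.0% | 20.0 | 0.56 | 54% | 45% |
| 10% | 47.8% vs 28.9% | 18.9 | 0.60 | 48% | 39% |

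**5. False negatives only (Sp = 1, Se = 0.90).** The observed risks are 0.42 × 0.90 = 37.8% and 0.21 × 0.90 = 18.9%. The risk ratio stays at 0.50 and only the difference shrinks, to 18.9 points. Movement of the risk ratio towards 1 is thus specific to false positives. Shrinkage of the risk difference occurs with either kind of error.

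**The case against.** The strongest reply is that eligibility already does most of the work. Everyone enrolled has been screened for chronic pain, the pre-existing pain most likely to be mistaken for CPSP months later, and the definition also requires other causes to be excluded. A false positive then needs non-chronic preoperative pain that persists unchanged to 3 months or beyond, is forgotten or misdescribed by the patient, and is not attributed to anything else. On that view the low end of the table is the realistic one, and the loss there is slight. This stands as a limit on size. It does not supply the missing comparison for the patients who remain.

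A reader might infer three stronger things, none of which the documents support:

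- **That classification must be by recall.** The protocol is silent on method. Screening, comorbidity and QoR-15 data are taken before surgery, and the items of QoR-15 are not listed, so some pain content cannot be ruled out. What can be said is that no record of site or character is scheduled.
- **That the CPSP effect is diluted.** This is a conditional expectation. It requires error that does not differ by arm, which blinding makes plausible, and no error rate is given. Step 5 shows that false negatives alone leave the risk ratio unchanged.
- **That the missing baseline is what makes the trial small for CPSP.** In the illustration, power is about 50% at 38 per arm with perfect classification. Sample size accounts for most of that shortfall.

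**Conclusion.** The point holds in a limited form. The definition depends on preoperative pain, and for non-chronic pain the schedule provides nothing to judge it against. Some CPSP may be misclassified at 3, 6 and 12 months.

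The size cannot be derived from the documents. Under the assumed 42% versus 21%, with false positives only and equal error in both arms, the risk ratio moves from 0.50 to 0.51–0.53 at 1–3% error and to 0.60 at 10%. Given the chronic-pain exclusion, the effect may well be small.

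The tension between the Introduction's primary aim and the secondary status of CPSP in Outcome measures is a separate matter and does not make this point more serious. It is worth acting on because the remedy is cheap and the information cannot be recovered after surgery.

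**What to change.** Add a baseline row to Appendix A. When the preoperative QoR-15 is completed, record any current or recent pain: presence, site, NRS and character. State in Outcome measures that the blinded assessor classifies CPSP at 3, 6 and 12 months against this record.

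Baseline SF-MPQ-2 and BPI are optional. Outcome measures uses them to grade severity and impact in patients who report CPSP, so the definition does not need them before surgery.

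The cost is a few minutes per patient at an existing contact and one row in the schedule. Treatment and sample size do not change. Patients enrolled before the change would lack the record, so the report should state how many there are and how their CPSP was classified.

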While regional anaesthesia is crucial for managing acute postoperative pain, its impact on CPSP remains largely unknown. The potential for regional anaesthesia to reduce CPSP has been identified as one of the top research priorities in anaesthesia and perioperative care. Intertransverse process block (ITPB) is a novel and promising alternative, targeting the paravertebral space through extra-paravertebral injection within the intertransverse tissue complex, posterior to the superior costotransverse ligament (SCTL). Recent MRI studies have demonstrated consistent spread of local anaesthetic to the ipsilateral intercostal, paravertebral spaces, neural foramina, and epidural space following ITPB, suggesting potential for both somatic and visceral analgesia. It demonstrated preferential spread of LA to the epidural space and neural foramina over the ESPB, and into the thoracic paravertebral space with effective analgesia after breast and video-assisted thoracoscopic surgeries. Compared to other regional techniques in cardiac surgery, ITPB may offer a simpler and safer approach with reduced risk of pleural puncture and bleeding. Therefore, this trial will assess the analgesic efficacy of ITPB aimed at mitigating both acute and chronic postsurgical pain in cardiac surgical patients. We hypothesis ITPB will reduce CPSP after cardiac surgery, improve pain control, improve quality of recovery and health-related quality of life. The primary aim is to investigate the efficacy of intertransverse process block (ITPB) on CPSP after cardiac surgery by determining the incidence of CPSP at 3-month, defined as persistent pain that was not present before surgery or that had different characteristics, and other possible causes of pain are excluded. The secondary aims are to investigate the quality of recovery after cardiac surgery, and its analgesic efficacy in the immediate postoperative period, and to investigate the efficacy of ITPB on the incidence of CPSP at 6-month and 12-month, and the pain interference (sensory and affective components, physical activities) at 3-month, 6-month and 12-month after surgery.

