### ***Statistics and sample size calculation***

Sample size was calculated using G\*Power software version 3.1.9.3 (Kiel University, Kiel, Germany), based on the QoR-15 score at 24 hours postoperatively — the primary outcome. The minimum clinically important difference (MCID) for the QoR-15 score is eight points, and the typical standard deviation (SD) ranges from 10 to 16. Assuming a two-sided type I error of 0.05, type II error of 0.2, and a population variance of 144 (SD = 12), a sample size of 36 per group is required. Allowing for a 20% dropout rate as a result of loss to follow up after patients discharge, a total of 96 patients (48 patients per group) will provide 80% power to detect a mean difference of  $\geq 8$  points in the QoR-15 score at 24 hours between the two groups.

All outcomes will be analyzed and reported on an intention-to-treat basis, with patients analyzed according to their randomized group regardless of protocol adherence. A secondary per protocol analysis will be conducted for patients who do not adhere fully to the study protocol. Given the repeated measures of pain scores over time, which are correlated,

Generalised Estimating Equation (GEE) models will be used to assess the time effects of postoperative analgesia. Categorical data will be reported as counts and percentages. Continuous variables will be presented as mean (standard deviation) or median (interquartile range), depending on normality assessed using the Shapiro-Wilk's test. Between-group comparison will be conducted using the independent sample *t*-test for parametric data and Mann-Whitney U test for nonparametric data. Categorical variables will be compared using the Chi-square test. Data analyses will be performed using SPSS 27.0 (IBM Corp, Armonk, NY), and GEE modelling will be conducted using Stata V.14 (Statam College Station, Texas, USA), with a Gaussian distribution, identify-link function, exchangeable correlation structure, and robust standard errors. A P-value of  $<0.05$  will be considered statistically significant, without adjusting for multiple comparisons.

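### Read plainly, the protocol collects SF-MPQ-2 and BPI interference from patients who report CPSP, so a between-arm test of these scores would not compare the randomised groups

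*Protocol*

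**What the plan says.** In the protocol's Outcome measures section, the secondary outcomes include "pain interference measured with Short-Form McGill Pain Questionnaire-2 (SF-MPQ-2) and Brief Pain Inventory (BPI) Interference Scale at 3-month, 6-month and 12-month after surgery". That entry is not limited to any subset of patients. The next paragraph defines CPSP and then says who goes on to be measured: "Participants reported CPSP will further be assessed on the severity and impact of chronic pain", naming SF-MPQ-2 and BPI as the instruments. The Data collection section is in line with this: "The SF-MPQ-2 and Brief Pain Inventory will be used to evaluate the CPSP at 3-month, 6-month and 12-month after surgery".

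Two other places point the other way. The Appendix A grid marks both instruments at 3 and 6 months with no footnote or condition (it has no 12-month column). The Statistics section states "All outcomes will be analyzed and reported on an intention-to-treat basis", keeping each patient in the arm assigned. For tests it says "Between-group comparison will be conducted using the independent sample" t-test, or the Mann-Whitney U test when data are not normal.

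Nowhere does the protocol assign a score to a patient without CPSP, or describe these scores as descriptive within CPSP cases. The Introduction gives the expected effect on the gating event itself: "We hypothesis ITPB will reduce CPSP after cardiac surgery".

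**The concern.** Whether a patient reports CPSP is known months after randomisation, and the block is expected to change it. If reporting CPSP is the gate to the questionnaires, the patients in whom the block prevented chronic pain have no score, and those who remain have been selected differently in the two arms.

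A test among reporters then asks how severe CPSP is in those who still have it. It does not ask what ITPB does to pain interference, which the Introduction names as a secondary aim, and it cannot satisfy the intention-to-treat statement. A real benefit could look smaller, absent or, in some circumstances, like harm. The scores would also come from a small part of the sample.

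**Working it through.** **Inputs from the protocol.** 48 per arm; 20% dropout; SD 12 and an 8-point difference for QoR-15; "Assuming a two-sided type I error of 0.05, type II error of 0.2"; and CPSP "prevalence rates ranging from 28% to 56% in the years following surgery", used here as the control-arm range.

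**Assumed inputs.** All score values, severity splits, latent-pain distributions and reductions in CPSP. The protocol gives none of these.

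**The plan's own figure.** n per group = 2 × (1.96 + 0.84)² × 144 / 8² = 2 × 7.85 × 2.25 = 35.3, so 36, as stated. That figure is for QoR-15; none is given for SF-MPQ-2 or BPI. After dropout, 48 × 0.8 = 38.4, so about 38 per arm are followed.

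**Patients with scores = followed patients × CPSP rate.**
- Control: 38 × 0.28 = 10.6 to 38 × 0.56 = 21.3.
- ITPB, if CPSP is halved: 5.3 to 10.6.

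**Direction of the comparison.** Mean score among reporters, and over all patients with no CPSP scored 0:

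| Assumed scenario | Reporters: control v ITPB | All patients: control v ITPB |
|---|---|---|
| A. CPSP 40%, half mild (2) and half severe (6); block prevents half the mild cases | 4.00 v 4.67 | 1.60 v 1.40 |
| B. As A, but block halves CPSP regardless of severity | 4.00 v 4.00 | 1.60 v 0.80 |
| C. Latent pain SD 3, CPSP 40%; every patient shifted down 1 point | 2.14 v 1.86 | 0.86 v 0.52 |

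Arithmetic for A:
- Control reporters: (0.20 × 2 + 0.20 × 6) / 0.40 = 4.00.
- ITPB reporters: (0.10 × 2 + 0.20 × 6) / 0.30 = 4.67.
- All patients: 0.40 × 4.00 = 1.60 and 0.30 × 4.67 = 1.40.
- With control CPSP of 28% the all-patient means are 1.12 v 0.98, and with 56% they are 2.24 v 1.96. The reporter means do not change.

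In C the direction is right, but the relative reduction is 0.28/2.14 = 13% among reporters against 0.34/0.86 = 40% over all patients.

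**Simulation of A** (38 or 48 per arm, control CPSP 28%, 40% or 56%, 4000 runs each; mild scores with mean 2 and SD 0.8, severe with mean 6 and SD 1.5). The reporter mean was worse under ITPB in 73% to 84% of trials, and significantly worse (t-test, p < 0.05) in 9% to 16%, although no simulated patient was harmed. The all-patient mean favoured ITPB in 62% to 69%.

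**Power under a uniform shift** (latent mean −0.6, SD 3, floor at 0, ITPB shifted by −1.5, 38 per arm; CPSP 42% v 24%). Mann-Whitney power was about 8% among reporters and about 41% over all patients. Reporter means were about 2.19 v 1.77, the correct direction. The ITPB mean was the worse one in about 26% of runs, and significantly so in under 1%.

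**How much of the 41% is incidence?** For 42% v 24% with 38 per arm, SE = √[(0.42 × 0.58 + 0.24 × 0.76)/38] = 0.106. Then 0.18/0.106 − 1.96 = −0.26, which is about 40% power for the proportions alone. The all-patient test therefore largely carries the difference in CPSP incidence.

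**The case against.** **The restriction is not written outright.** A reader might infer that the protocol gives the questionnaires exclusively to CPSP reporters. It does not use that word; the outcome list and the Appendix A grid are unrestricted, and intention to treat covers all outcomes. This stands as a limit on certainty. But the sentence in Outcome measures is the only one that says who is assessed, and Data collection supports it. If everyone was meant, that sentence still needs correcting.

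**The scoring rule may be in the SAP.** How a patient without CPSP is scored can reasonably be left there, and the protocol does not say the test is confined to reporters. This stands in part. A SAP could assign zeros to patients with no pain, but it cannot recover questionnaires never given. The CPSP definition excludes pain with another cause, so a patient without CPSP may still have pain and no score.

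**Reversal needs a particular assumption.** A reader might infer that the comparison will point the wrong way. The documents do not support that: nothing in them says the block spares mainly mild cases, and a uniform shift keeps the right direction. This stands. Attenuation and loss of power are the safer claims.

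**The all-patient score overlaps with incidence.** This also stands. CPSP incidence is already a secondary outcome at the same visits, so the gain in power is mostly not new information about interference. Severity among those with CPSP remains a legitimate descriptive question.

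**Conclusion.** The concern holds in limited form. On the plain reading of Outcome measures and Data collection, the two instruments are collected from patients who report CPSP. That conflicts with their unrestricted listing, with the Appendix A grid and with the intention-to-treat statement. A between-arm test on those data is not a randomised comparison. Depending on which cases the block prevents, it may shrink a benefit (scenario C), erase it (B) or reverse it (A). The sizes rest on the assumed scores and effects. The counts of scored patients rest on the quoted prevalence range applying to the control arm and on CPSP being halved.

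The consequence is confined to secondary outcomes. QoR-15 at 24 hours, its sample size and the CPSP incidence comparison are untouched. A reader might also infer that a preoperative pain-interference measure is needed; that is a separate matter, partly covered by the exclusion of patients with a chronic pain history, and is not part of this point.

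**What to change.** 1. Amend Outcome measures and Data collection so that SF-MPQ-2 and BPI interference are given to all randomised patients at 3, 6 and 12 months, and bring the Appendix A grid into line.
2. At minimum, prespecify a score of 0 for patients who are contacted and report no pain at all, and give the questionnaires to anyone with any pain, whether or not it meets the CPSP definition. Patients not reached remain missing and are not scored 0.
3. Make the comparison over all randomised patients the intention-to-treat analysis of these outcomes, and label the CPSP-only summary descriptive. State that the all-patient score partly reflects CPSP incidence.

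The cost is protocol wording and a few questionnaire minutes per contact, less under option 2. The change should be in place before the first 3-month follow-up, since scores not collected then cannot be obtained later.
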